### Aims and research questions

The study aims to explore the differences between a 40-hour block SCP experience and a 40-hour block TCP experience in terms of development of professional competencies and fieldwork confidence, and to determine the comparative delivery costs for the SCP and TCP programs as borne by the university.

The research questions are:Do students who undertake an SCP in the early years of an entry-level occupational therapy program achieve *non-inferior outcomes* in their development of professional practice skills compared with those who attend a TCP, as assessed by a post-placement written examination (primary outcome), Student Practice Evaluation Form-Revised (SPEF-R) evaluation [31, 32] and end-of-semester study unit score?Do students and supervisors report similar professional practice learning opportunities when students complete an SCP compared to those students who complete a TCP, assessed using a self-report survey, and similar frequencies of *not applicable* and *insufficient observation* items in the SPEF-R?Economic research questions: If non-inferiority is established, does SCP cost less than TCP from the perspective of (1) the health sector and (2) the universities as providers?If costs of SCP are not less than those of TCP, are there offsetting benefits which still make the SCP value for money?
Do students who experience an SCP in the early years of an entry-level occupational therapy program report self-confidence outcomes that are non-inferior to those who attend a TCP, as measured by the Student Confidence Questionnaire [33]?What are the perceptions of quality and adequacy of the TCP versus SCP experience of students and clinical educators?

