#### Sample size

The SCP has been trialled at the managing university within a second-year level unit of study in an undergraduate occupational therapy bachelor degree. This provided a set of indicative student outcomes allowing for calculation of a sample size estimate. The primary outcome used for this calculation was the post-placement examination score (range 0–100%). Non-inferiority was defined as a mean score difference in exam scores between SCP and TCP groups of ≤7%. This value was based on the standard deviation of student examination scores obtained within the unit of study where the SCP was piloted in 2013.

Using standard power estimate criteria (to achieve a power of at least 0.8, alpha level 0.05), 120 students per group are required (total sample = 240). To account for clustering according to university site, where an average cluster size of 50–60 students is anticipated, and an estimated intraclass correlation coefficient (ICC) of 0.007, an additional 100 students will be required (*n* = 340). Finally, to allow for a 20% attrition rate (340/0.8), a total sample of 425 participants is required.

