Individual student performance on each item is rated on a 5-point scale as follows: 1. *Performs unacceptably*; 2. *Experiencing difficulty or performs marginally*; 3. *Performs adequately*; 4. *Performs proficiently*; and 5. *Performs with distinction*. Scores of 1 or 2 indicate a failing performance. Students must pass all core units in each of the four domains of the SPEF-R to achieve an overall pass in the placement. Data will be collated to determine whether students pass overall, which domains are passed and the sum of the individual item scores in the SPEF-R. The frequencies of items identified as *not applicable* and *insufficient observation* in the SPEF-R will also be determined for each student. The student and supervisor reports of comparable learning experiences in each placement setting will be compared using data extracted from the SPEF-R and a self-report survey (research question 4).

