#### Statistical analyses methods

All data will be entered into a purpose-designed REDCap (https://projectredcap.org/) database, cleaned and assessed for missing data. Summary statistics will be used to describe the sample. To evaluate whether students who attend an SCP achieve non-inferior outcomes to those who attend a TCP, differences in achievement on the post-placement examination score will be evaluated using analysis of covariance (ANCOVA). A mean difference of ≥7 points on the examination score between students will be considered an educationally meaningful difference. Covariates included in the analyses will include broad placement type (vocational rehabilitation, physical rehabilitation or mental health) and any demographic variables identified as important during baseline analyses. Secondary outcomes related to whether students who attend an SCP achieve non-inferior outcomes to those who attend a TCP will be assessed using odds ratios between groups in predicting overall pass/fail grades on the SPEF-R, evaluated using binary logistic regression. Independent variables included in the analyses as possible covariates will include gender, age, broad placement type and any demographic variables identified in baseline analyses as important. Differences between SCP and TCP groups in achievement of a pass/fail grade on each of the four completed sections of the SPEF-R will be assessed using chi-square tests. Scores between SCP and TCP groups for individual SPEF-R items (scored on a 5-point ordinal scale) will be compared using a Mann-Whitney *U* test. An overall difference >1 point on the 5-point scale between groups will be considered educationally important.

To evaluate whether students and clinical educators report similar professional practice learning opportunities during SCP compared to TCP, the differences in frequencies of *not applicable* and *insufficient observation* items checked in the total SPEF-R by (1) students and (2) clinical educators will be compared using an independent samples *t* test, using 95% confidence intervals of the estimated mean difference between groups to identify differences.

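### Above item level the SPEF-R arms are compared only on pass/fail: no planned analysis estimates the overall 5-point difference the plan calls important

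*Protocol article*

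**What the plan says.** **The question.** In the Protocol article, Aims and research questions, the first question asks whether SCP students do no worse than TCP students in professional practice skills, "as assessed by a post-placement written examination (primary outcome), Student Practice Evaluation Form-Revised (SPEF-R) evaluation" and the unit score.

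**The instrument.** The Student Practice Evaluation Form-Revised section describes four domains with 5 + 5 + 3 + 5 = 18 items, each rated 1 to 5. On the pass cut it says: "Scores of 1 or 2 indicate a failing performance". Overall pass depends on the core items. The data to be collated are overall pass, "which domains are passed and the sum of the individual item scores in the SPEF-R".

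**The analysis.** Statistical analyses methods plans three SPEF-R comparisons of performance:

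- Overall: the secondary non-inferiority outcomes "will be assessed using odds ratios between groups in predicting overall pass/fail grades on the SPEF-R, evaluated using binary logistic regression".
- By domain: "achievement of a pass/fail grade on each of the four completed sections of the SPEF-R will be assessed using chi-square tests".
- By item: "Scores between SCP and TCP groups for individual SPEF-R items (scored on a 5-point ordinal scale) will be compared using a Mann-Whitney" U test.

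It then adds: "An overall difference >1 point on the 5-point scale between groups will be considered educationally important". The Abstract names the proportion passing the placement as a secondary outcome.

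**The concern.** The overall and domain-level comparisons use only the cut between grades 2 and 3. Adequate, proficient and distinction-level performance therefore count as the same result. The graded information enters only through 18 separate rank tests. These give 18 p-values, but no SPEF-R or domain estimate, no confidence interval and no rule for reading them together.

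Two items in the protocol are left without a counterpart. The collated item sum has no between-group comparison. The threshold for an overall difference on the 5-point scale refers to a quantity that none of the three analyses produces.

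The SPEF-R is the supervisor's rating of behaviour and communication observed on placement, which the written examination does not measure directly. If most students pass, a moderate loss on it could leave similar pass rates and a scatter of item p-values with no agreed reading. In a non-inferiority setting, an insensitive comparison tends to favour the new arm.

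**Working it through.** **1. Sample size to use.** The Sample size section starts from 240 students. With clusters of 60 and an ICC of 0.007, 240 × (1 + 59 × 0.007) = 339.1, so 340. Then 340 / 0.8 = 425. Both figures match the protocol. The 340 evaluable students give 170 per arm. This calculation concerns the examination; the protocol gives no power figure for the SPEF-R.

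**2. What each planned analysis delivers.**

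| Analysis | Scale used | Overall or domain estimate on the 1–5 scale? |
|---|---|---|
| Logistic regression, overall | pass/fail | no |
| Chi-square, four domains | pass/fail | no |
| Mann-Whitney, 18 items | 1–5 | no, item by item only |
| Item sum | collated | not compared |

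**3. Pass/fail against a full-scale score.** The protocol gives no pass rate, so this step rests on assumptions: one underlying normal scale with a cut, 170 per arm, two-sided 0.05, TCP pass rate *p* of 90–98%, and SCP lower by *d* SD.

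- SCP pass rate: q = Φ(Φ⁻¹(p) − d)
- Pass/fail power: 1 − Φ(1.96 − (p − q) / √[(p(1−p) + q(1−q)) / 170])
- Full-scale power: 1 − Φ(1.96 − d / √(2/170))

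For d = 0.3, the full-scale ratio is 0.3 / √(2/170) = 2.766, giving power 0.790.

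| TCP pass rate | SCP pass rate | Pass/fail power | Full-scale power | Failures, both arms |
|---|---|---|---|---|
| 98% | 96.0% | 0.187 | 0.790 | 10.2 |
| 95% | 91.1% | 0.298 | 0.790 | 23.7 |
| 90% | 83.7% | 0.409 | 0.790 | 44.7 |

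For d = 0.2, pass/fail power is 0.102, 0.151 and 0.203, against 0.454.

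**4. What the item tests add.** These results come from simulations with assumed item distributions.

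- *One full grade lower for every SCP student:* power for a single item is about 1.00 at 120 or 170 per group. If all TCP ratings are 4 or 5, pass/fail has power 0, because nobody fails even after the drop.
- *Shift of 0.3 item SD, 18 items, inter-item correlation 0.4 or 0.6, 170 per arm:* each item test has 65–71% power. At least one item survives Bonferroni correction in 79–93% of runs. A t test on the mean item score has 90–100% power and pass/fail 24–58%.
- *Shift of 0.2 SD:* the item tests after Bonferroni have 50–57% power, against 66–80% for the mean score. Without correction, the 10th to 90th percentile range for significant items is about 0 to 15 of 18.
- *No true difference:* two sets of simulations gave at least one item at p < 0.05 in 38–47% and about 45–51% of trials.

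The item tests are therefore sensitive, but an uncorrected set often flags something by chance, and a corrected set is less powerful than one mean score.

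**The case against.** The strongest objection is that the graded scale is already used. The item tests follow the pass/fail analyses in the same section, and they are sensitive. A reader might infer that the SPEF-R is analysed only as pass/fail, so that SCP could be a whole grade worse with nothing to show for it. The protocol does not support that: such a drop would appear on the affected items almost with certainty. Nor should the gap between 19–41% and 79% be read as the gain over the whole plan, since it leaves out the item tests. This part of the objection stands.

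Second, passing is the declared secondary outcome and follows the instrument's own competence rule; it is not an arbitrary cut. That also stands, and it is a reason not to demote pass/fail.

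Third, naming a test for a derived total can be left to an analysis plan that is not shown. That would answer the bare absence of a test on the sum. It does not answer the text as published, which sets a threshold for an overall difference that none of its listed analyses estimates.

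Fourth, a reader might infer that the logistic model will be overloaded. The protocol lists only possible covariates and gives no pass rate, so the failure counts above are conditional. The model would be fragile at high pass rates, but the protocol does not show that these will occur.

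**Conclusion.** The point holds in a limited form. For the non-inferiority question, every overall and domain-level SPEF-R comparison is on pass/fail. The collated item sum is not compared, and the overall 5-point difference that the plan calls important is not estimated. The 18 item tests would reveal a large drop, but they give no single estimate, interval or combined reading.

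The size depends on assumptions. With 170 per arm, pass rates of 90–98% and a 0.3 SD shift, pass/fail has 19–41% power against 79% for a full-scale score. Against the item tests the gain is smaller: at 0.2 SD, 66–80% for the mean score against 50–57% after Bonferroni correction. Item distributions, correlations and pass rates are all assumed, and these powers are for tests of difference, not of non-inferiority.

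This is a secondary outcome. The examination analysis is unaffected.

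**What to change.** In Statistical analyses methods:

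- Keep overall pass/fail as the declared secondary outcome.
- Add a between-group comparison of the mean score over rated items (1 to 5), overall and for each of the four domains, using the same adjusted linear model as the examination score.
- Report the SCP minus TCP difference with its 95% confidence interval, read against the plan's own 1-point threshold.
- Label the 18 item-level tests as descriptive.
- Report the number of rated items by arm.

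The 1-point threshold is stated as a mark of educational importance. The protocol's explicit definition, "Non-inferiority was defined as a mean score difference in exam scores between SCP and TCP groups of ≤7" percent, concerns the examination. The added interval therefore informs the SPEF-R question but does not by itself create a SPEF-R non-inferiority margin.

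The cost is wording, since all item scores are already collected. There are three downsides. A mean score treats the grades as equally spaced. Items marked not applicable or insufficiently observed may differ by arm, so the means could cover different items; this is why the rated-item counts are needed. Supervisors are unblinded, as they already are for pass/fail.

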**Methods/design:**

This study is a pragmatic, non-inferiority, single-blind, multicentre, two-group randomised controlled trial (RCT) with an embedded economic analysis. The RCT will compare a block of 40 hours of simulated placement (intervention) with a 40-hour block of traditional placement (comparator), with a focus on student learning outcomes and delivery costs. Six universities will instigate the educational intervention within their respective occupational therapy courses, randomly assigning their cohort of students (1:1 allocation) to the simulated or traditional clinical placements. The primary outcome is achievement of professional behaviours (e.g. communication, clinical reasoning) as assessed by a post-placement written examination. Secondary outcomes include proportions passing the placement assessed using the Student Practice Evaluation Form-Revised, changes in student confidence pre-/post-placement, student and educator evaluation of the placement experience and cost-effectiveness of simulated versus traditional clinical placements. Comprehensive cost data will be collected for both the simulated and traditional placement programs at each site for economic evaluation.

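### SPEF-R pass is framed as proportions passing and a non-inferiority question, but the domain analysis yields no interval, and the overall odds ratio can fail or be very wide if fails are rare

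*Protocol article*

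**What the plan says.** The abstract of the protocol article states: "Secondary outcomes include proportions passing the placement assessed using the Student Practice Evaluation Form-Revised". Research question 1, under Aims and research questions, lists the SPEF-R evaluation beside the written examination among the outcomes on which SCP should be non-inferior.

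Under Statistical analyses methods, overall pass "will be assessed using odds ratios between groups in predicting overall pass/fail grades on the SPEF-R, evaluated using binary logistic regression". The "possible covariates will include gender, age, broad placement type and any demographic variables identified in baseline analyses as important". Group differences "in achievement of a pass/fail grade on each of the four completed sections of the SPEF-R will be assessed using chi-square tests". Individual item scores are compared by Mann-Whitney tests.

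The pass rule is in the SPEF-R section: "Students must pass all core units in each of the four domains of the SPEF-R to achieve an overall pass in the placement", and "Scores of 1 or 2 indicate a failing performance".

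The only non-inferiority margin is for the examination: "Non-inferiority was defined as a mean score difference in exam scores between SCP and TCP groups of ≤7" (per cent). No margin for SPEF-R pass appears on any scale, and no expected pass or fail rate is given.

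**The concern.** The planned results do not line up with the question asked of them. Non-inferiority is judged by whether a confidence limit excludes an unacceptable deficit. For the domains the plan names a test that returns a p-value and no limit. For overall pass it names an odds ratio, which is one step removed from the stated outcome and behaves badly when one outcome category is nearly empty.

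A university deciding whether to substitute simulation needs to know how many more students, at most, might fail under SCP. Non-significant domain tests do not say. If fails are few, the odds ratio may say only that the data are compatible with almost anything, although the same counts limit the absolute difference to a few percentage points.

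**Working it through.** **Inputs.** The Sample size section gives 340 students after allowance for clustering and before inflation for attrition (340/0.8 = 425). Allocation is 1:1, so 170 per arm are analysed. The fail rate f is an assumption, varied from 1% to 10%, with the same true rate in both arms. Clustering by site and covariates are ignored. The plan prints no SPEF-R figure to reproduce.

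**1. What a chi-square result can show.** With 3 v 3 fails and with 17 v 17 fails (170 per arm), chi-square is 0 and p = 1 in both cases. The 95% Newcombe intervals for the difference are ±3.5 and ±6.5 percentage points. The same p-value therefore goes with quite different limits on how much worse SCP could be. This holds at any fail rate.

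**2. Chance that an arm has no fails.** P(at least one arm with zero fails) = 1 − (1 − (1 − f)^170)².

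| True fail rate | (1 − f)^170 | P(at least one arm with zero fails) |
|---|---|---|
| 1% | 0.181 | 33% |
| 2% | 0.032 | 6% |
| 3% | 0.0056 | 1% |
| 5% | 0.00016 | under 0.1% |

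With zero fails in one arm the maximum-likelihood odds ratio is zero or infinite, and with zero in both it is undefined. With 2 v 0 fails, for example, the odds ratio is infinite, while the difference is 1.2 points (Newcombe 95% interval −1.2 to 4.2).

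A simulation of 1,000 trials per rate fitted arm, gender, age and two placement-type terms, assuming 12% men and equal streams. The arm odds ratio was non-finite in 30%, 6%, 1%, 0% and 0% of trials at fail rates of 1%, 2%, 3%, 5% and 10%, in line with the table.

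**3. Precision when both arms have fails.** With e fails in each arm, the 95% odds ratio interval is exp(±1.96 × √(2/e + 2/(170 − e))). For e = 3: √(0.6667 + 0.0120) = 0.824, giving 0.20 to 5.03. The Newcombe half-width combines the Wilson limits of the two arms. For 3/170 = 1.76% these are 0.60% and 5.06%, so √((5.06 − 1.76)² + (1.76 − 0.60)²) = 3.5 points.

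| Fails per arm | Rate | Odds ratio 95% interval | Difference 95% interval (points) |
|---|---|---|---|
| 3 | 1.8% | 0.20 to 5.03 | ±3.5 |
| 5 | 2.9% | 0.28 to 3.52 | ±4.1 |
| 9 | 5.3% | 0.39 to 2.58 | ±5.1 |
| 17 | 10% | 0.49 to 2.03 | ±6.5 |

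**4. Does the chi-square test itself break down?** Enumerating all outcomes with 170 per arm gives the actual error of a nominal two-sided 5% test.

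| True fail rate | Pearson chi-square | Fisher exact |
|---|---|---|
| 1% | 3.5% | 0.3% |
| 2% | 4.5% | 1.4% |
| 3% | 4.6% | 2.0% |
| 5% | 4.9% | 2.6% |
| 10% | 5.2% | 3.2% |

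The chi-square test keeps its size closely enough. The objection to it is the missing interval.

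**The case against.** Logistic regression is a standard way to compare proportions, the covariates are only possible ones, and a sparse-data fallback or a model-based risk difference may stand in an analysis plan that is not shown. This is fair, and the choice of logistic regression is not an error.

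Rare fails are also an inference. A rating of marginal counts as a fail, and a student must pass 4 + 2 + 2 + 4 = 12 core items, which pushes the overall fail rate up. On the other side, this is a one-week, early-year placement with a reduced form. The documents do not settle it, so the sparse-data point stays conditional.

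The narrower look of the difference scale partly reflects the low base rate. A difference of 3.5 points above 1.8% is itself an odds ratio of about 3.1. The difference adds no information, but it stays estimable and is in the units of the stated outcome.

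A reader might infer three stronger things that the documents and the calculations do not support:

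- **That the adjusted model will usually fail.** Some coefficient was non-finite in 87%, 56%, 33%, 15% and 2% of simulated trials at fail rates of 1%, 2%, 3%, 5% and 10%. Most of these concern a gender or stream term, not the comparison of arms.
- **That chi-square is invalid once expected counts fall below 5, so Fisher's exact test should replace it.** The enumeration shows the opposite trade-off.
- **That a difference in proportions alone would settle non-inferiority.** It would not without a margin.

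What remains untouched is that a domain test of difference, with no interval, cannot answer a non-inferiority question.

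**Conclusion.** The point holds in a limited form. The absence of an interval for the domain comparisons is independent of the fail rate. The weakness of the overall odds ratio depends on it. At an assumed 1% to 2% the odds ratio is undefined or infinite in roughly 33% to 6% of trials and very wide otherwise. At 5% or more it is finite and only moderately imprecise. These figures assume 170 evaluable students per arm, equal true fail rates and no clustering. The matter concerns a secondary outcome and leaves the examination analysis and the sample size as they are.

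**What to change.** Make the main SPEF-R pass result the SCP minus TCP difference in proportions passing, overall and for each of the four domains, with a 95% Miettinen-Nurminen or Newcombe interval. State in advance a margin for SPEF-R pass on that scale, with its reason, and read the interval against it. Keep the covariate-adjusted odds ratio as support, with Firth penalisation if fails turn out sparse. The chi-square tests may stay beside the intervals and should not be replaced by Fisher's exact test.

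The cost is a change of wording in the analysis section and the work of justifying a margin. The downside is that the main secondary figure is less adjusted for covariates.

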#### Placement experience

*Student* placement experiences will be assessed using survey and focus group methods after the completion of the placement. Survey data will be collected using the 7-item SPEF-R companion instrument that asks the student to rate their experience of being oriented to the placement organisation, how welcome they felt within the workgroup, whether the clinical educator’s expectations were clear, whether they felt supported and how they felt about the evaluative experience. Responses are indicated using a 5-point Likert scale ranging from 1 = *strongly disagree* to 5 = *strongly agree*. Summed responses provide scores ranging from 7 to 35. In addition, a 14-item survey designed to assess student satisfaction with placement will be completed by students of both placement types, as the questions are generic [38]. This survey also employs a 5-point Likert scale ranging from 1 = *strongly disagree* to 5 = *strongly agree*. In addition to survey data, participating students will be invited to contribute to a focus group in which their perceptions of the meaning, value and quality of their placement experiences will be explored.

*Supervisor and educator* perceptions of SCP and TCP opportunities will be assessed using an online survey developed to mimic the placement experience questions posed to students. Responses to the questions will be indicated using a 5-point Likert scale ranging from 1 = *strongly disagree* to 5 = *strongly agree*. Educators involved in the delivery of the placement experiences will also be invited to contribute to focus groups that explore their perceptions of satisfaction and quality of the placement for early years’ occupational therapy students.

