To evaluate whether students who experience an SCP report non-inferior levels of confidence during placement outcomes compared to those who experience a TCP, the difference between change scores on the confidence questionnaire between SCP and TCP groups will be assessed using an independent samples *t* test. Between-group analyses of mean total score differences on this questionnaire, both pre- and post-SCP and TCP, will be determined using independent samples *t* tests. Within-group differences will be established using paired samples *t* tests.

To assess students’, educators’ and supervisors’ placement experiences, data from the SPEF-R student review of professional practice placement survey, Student Evaluation of Placement questionnaire, and Clinical Educator Evaluation of Placement questionnaire will be summarised and reported descriptively. The 5-point Likert-style item responses on each questionnaire will be reported graphically. Differences in item ratings between groups of participants will be assessed using independent samples *t* tests*.* Additional thematic analyses will be carried out on written comments made on any of the instruments in conjunction with data obtained through focus group interviews. All qualitative data will be analysed inductively to address the question of perceived placement value and quality.

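### The secondary plan tests SPEF-R items and domains, and survey items it also calls descriptive, one by one, while the defined SPEF-R sum and 7–35 review total are never compared between arms

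*Protocol article*

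**What the plan says.** All references are to the protocol article.

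- **SPEF-R items** (Statistical analyses methods): "Scores between SCP and TCP groups for individual SPEF-R items (scored on a 5-point ordinal scale) will be compared using a Mann-Whitney *U* test". The next sentence sets an overall between-group difference of more than 1 point on the 5-point scale as educationally important.
- **SPEF-R domains** (same section): "Differences between SCP and TCP groups in achievement of a pass/fail grade on each of the four completed sections of the SPEF-R" are to be assessed by chi-square tests.
- **Overall SPEF-R pass** (same section): one logistic regression on pass/fail.
- **Surveys** (same section): data from the student review, the student evaluation and the clinical educator evaluation "will be summarised and reported descriptively". Two sentences later: "Differences in item ratings between groups of participants will be assessed using independent samples *t* tests".
- **Totals**: the SPEF-R section says that data will be collated on "the sum of the individual item scores in the SPEF-R". The Placement experience section says of the 7-item student review: "Summed responses provide scores ranging from 7 to 35". The analysis section names no SCP–TCP comparison of either total.
- **Alpha**: the only level given is in the Sample size section, "to achieve a power of at least 0.8, alpha level 0.05". None is stated for the secondary tests.

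**The concern.** Three things in the text do not fit together.

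1. The SPEF-R is broken into its components and each is tested, while its collated sum is not analysed. The plan thus takes the route that produces the most chance findings and passes over a single comparison for which the data are already held.
2. The survey paragraph gives the item data two statuses. A reader cannot tell whether a small p-value on one satisfaction item is a description or a result.
3. The survey t-test sentence does not say which groups are compared. Its paragraph covers students, educators and supervisors, so the contrast could be SCP versus TCP, students versus educators, or both.

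At stake is the reading of the secondary research questions on SPEF-R performance and perceived placement quality. A few isolated items or domains with p < 0.05 could be presented as strengths or deficits of simulation, beside a primary result that they seem to support or contradict. Item-by-item testing is also weak where simulation shifts a whole instrument slightly and consistently.

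**Working it through.** **The plan's own figure.** The article states no family-wise error rate, so there is none to reproduce.

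**Counting the tests.**
- SPEF-R items (Student Practice Evaluation Form-Revised section): 5 + 5 + 3 + 5 = 18 Mann-Whitney tests.
- SPEF-R domains: 4 chi-square tests, so 18 + 4 = 22 SPEF-R tests.
- Student surveys (Placement experience section): 7 + 14 = 21 items, one t test each if the contrast is SCP versus TCP.
- Total: 22 + 21 = 43. This leaves out the educator survey items, the counts of not-applicable and insufficient-observation items, and the confidence tests.

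**Assumptions.** Two-sided 0.05 per test, carried over from the Sample size section. The documents give no correlation between test statistics, so a range of 0 to 0.7 is shown.

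**Expected false positives if the placements are identical** (number of tests × 0.05, whatever the correlation):
- SPEF-R: 22 × 0.05 = 1.1
- All: 43 × 0.05 = 2.15

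**Chance of at least one false positive.** If independent, 1 − 0.95^m:
- m = 22: 1 − 0.95^22 = 0.68
- m = 43: 1 − 0.95^43 = 0.89

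With one common correlation ρ, the statistics are written as √ρ·U + √(1−ρ)·E_i, with U and E_i independent standard normal. The chance is then 1 minus the average over U of [Φ((1.96 − √ρ·U)/√(1−ρ)) − Φ((−1.96 − √ρ·U)/√(1−ρ))]^m.

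| Correlation | 22 SPEF-R tests | 43 tests |
|---|---|---|
| 0 | 0.68 | 0.89 |
| 0.3 | 0.57 | 0.77 |
| 0.5 | 0.44 | 0.59 |
| 0.7 | 0.30 | 0.39 |

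If tests are correlated only within an instrument (blocks of 22, 7 and 14), the figure for 43 tests is 0.72 at 0.5 and 0.57 at 0.7.

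**The 1-point threshold.** With an assumed item SD of 1 and 120 per arm, the standard error of a difference is √(2/120) = 0.129. One point is 1/0.129 ≈ 7.7 standard errors, so a chance difference on a SPEF-R item would practically never reach it.

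**Power of a total against a single item.** Illustration for the 7-item review, assuming a uniform shift of 0.25 SD per item, inter-item correlation 0.5 and 120 per arm:
- One item: 0.25/0.129 = 1.94, power about 0.49.
- Total: the SD of the sum is √(7 + 42 × 0.5) = √28 = 5.29 item SDs and the shift is 7 × 0.25 = 1.75. The standardised shift is 1.75/5.29 = 0.33, and 0.33/0.129 = 2.56, so power is about 0.73.

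**The case against.** The best defence has four parts.

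**Multiplicity rules for secondary outcomes usually sit in the analysis plan, which is not shown.** This stands as far as it goes: the absence of a stated adjustment is not itself a fault here. It does not answer what the article does state, namely item-level tests with two defined totals left without a comparison, and a paragraph that calls survey data descriptive and then tests them.

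**The 1-point threshold guards against over-reading.** This stands for SPEF-R items, as the arithmetic shows. It is a threshold on the 5-point scale, so it does not apply to pass/fail domain tests, and no such threshold is given for the survey items. Nor does the article say that a significant but smaller item difference will be disregarded.

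**The surveys already carry a descriptive label and may not be SCP–TCP tests.** This partly stands. A reader might infer that the article gives no exploratory status to any of these tests. That goes too far, because the descriptive wording covers the surveys. No such label covers the 22 SPEF-R tests. The 43-test figure depends on reading the survey t tests as SCP versus TCP.

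**The main conclusions rest elsewhere.** This stands. There is one primary outcome, the examination. Overall SPEF-R pass has its own single regression, and confidence is analysed on total and change scores. A reader might infer that the non-inferiority conclusion is put at risk, but nothing in the article makes it depend on an item or domain test.

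**Conclusion.** The point holds as a moderate weakness of the secondary analysis. The article plans 22 component tests on the SPEF-R and up to 21 on student survey items, compares neither defined total between arms, and contradicts itself on whether survey items are described or tested.

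If each test is run at 0.05, which is inferred and not stated, about 1.1 false positives are expected from the SPEF-R tests. About 2.15 are expected from all 43 if the survey tests are SCP versus TCP. The chance of at least one is 30–68% for the SPEF-R and 39–89% for all 43, over common correlations of 0.7 to 0.

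A reader might infer that a chance finding is more likely than not. The documents do not support that as a flat statement, because they give no correlation. With a common correlation it holds for 43 tests at 0.5 but not at 0.7, and for the SPEF-R alone it already fails at 0.5. The primary examination analysis and the overall SPEF-R pass analysis are unaffected.

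**What to change.** In Statistical analyses methods:

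1. Base SCP–TCP inference on the instrument as a whole. For the SPEF-R, keep the logistic regression on overall pass and add one comparison of the SPEF-R score over rated items, since items may be marked not applicable or insufficiently observed. For the student review, compare the 7–35 total.
2. Report the 18 SPEF-R items, the 4 domains and the survey items as exploratory estimates with 95% confidence intervals, and state that no conclusion about SCP versus TCP rests on a single item.
3. Reconcile the descriptive and t-test sentences in the survey paragraph, and say which groups are compared.

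Holm or fixed-sequence control across the secondary instruments is optional.

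The cost is wording only, because the items and totals are already to be collected. The small downside is that no single item or domain difference could be claimed as established.
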